**Suspected unexpected adverse reactions by SOC and PT ([no. of events] no. of patients (pct of patients) )**

|                    |                |                 |                          |             |                                        |
|--------------------|----------------|-----------------|--------------------------|-------------|----------------------------------------|
| System Organ Class | Preferred term | etoricoxib N=10 | H56:IC31 TB vaccine N=11 | Control N=9 | etoricoxib and H56:IC31 TB vaccine N=8 |
| No observations    |                |                 |                          |             |                                        |

**Adverse events leading to study drug discontinuation by SOC and PT ([no. of events] no. of patients (pct of patients) )**

|                    |                |                 |                          |             |                                        |
|--------------------|----------------|-----------------|--------------------------|-------------|----------------------------------------|
| System Organ Class | Preferred term | etoricoxib N=10 | H56:IC31 TB vaccine N=11 | Control N=9 | etoricoxib and H56:IC31 TB vaccine N=8 |
| No observations    |                |                 |                          |             |                                        |

**Most frequent AEs (4 or more occurrences) by PT ([no. of events] no. of patients (pct of patients) )**

|                |                 |                          |             |                                        |
|----------------|-----------------|--------------------------|-------------|----------------------------------------|
| Preferred term | etoricoxib N=10 | H56:IC31 TB vaccine N=11 | Control N=9 | etoricoxib and H56:IC31 TB vaccine N=8 |
|----------------|-----------------|--------------------------|-------------|----------------------------------------|

## Supplementary Figure 2

[figure not shown]

**Supplementary Figure 2. Flow cytometry gating strategy for the identification of CD4+ T cell subsets corresponding to Fig. 2 b and c, Fig. 3 e and f and Fig. 4 e and f in the manuscript.** Representative dot plots from a single participant acquired following whole blood intracellular cytokine staining assay are shown for unstimulated samples and samples stimulated with Purified Protein Derivate (PPD), Early Secretory Antigenic Target 6 (ESAT-6), Antigen 85b (Ag85b) and Latency associated protein Rv2660c. We used a time gate to exclude events that showed inconsistent fluorescence during acquisition, followed by a wide lymphocyte gate in forward-scatter (FSC)/side-scatter (SSC) plots and singlet cells in FSC-area (FSC-A) and FSC-height (FSC-H). We then selected T-cells by CD3+ surface expression (AmCyan) followed by separation of CD4+ (APC-H7) and CD8+ (Alexa Fluor 488) subsets by a quadrant gate. Included cytokines IFN $\gamma$  (Brilliant Violet 421), IL2 (PE) and TNF $\alpha$  (APC) were analysed by Boolean gating. Individual single cytokine gates were set applying unstimulated controls.

### Supplementary Figure 3

[figure not shown]

**Supplementary Figure 3. Immunoregulatory effects of etoricoxib.** Effect of etoricoxib administered during the first 84 days of standard TB treatment on Mtb-specific IFN $\gamma$ + T-cells (Hypothesis 1, table 3) in response to Ag85, ESAT-6 and CFP10 summed, in the etoricoxib group (red) and controls (grey) measured by Fluorospot at day 0 (n: 17/20) and day 84 (n: 18/14). Plots are shown with median, interquartile ranges (IQR) and minimum/maximum values. As the study was planned as an exploratory hypothesis generating phase I/II trial, all group comparisons, including p-values were regarded hypothesis supporting and not interpreted as confirmatory. Adjustments for multiple testing were not performed but a hierarchical order of immunogenicity outcomes defined *a priori* (Supplementary Data pp. 6-7) was judged adequate to assign importance/interpret the results of the respective statistical tests. Immunogenicity readouts of primary priority were analyzed using median regression with treatment as only independent explanatory factor.

Supplementary Figure 4

Cytokine+ responses to ESAT-6

[figure not shown]

Cytokine+ responses to Ag85B

[figure not shown]

red=Etoricoxib, blue=H56:IC31, black=Controls, green=Etoricoxib+H56:IC31

**Cytokine+ responses to CFP-10**

[figure not shown]

**IFN $\gamma$ +IL2+ responses to Ag85B, CFP-10 and ESAT-6**

[figure not shown]

red=Etoricoxib, blue=H56:IC31, black=Controls, green=Etoricoxib+H56:IC31

### IFN $\gamma$ responses to Ag85B and ESAT-6

[figure not shown]

### IFN $\gamma$ +IL2+ responses to Ag85B and ESAT-6

[figure not shown]

red=Etoricoxib, blue=H56:IC31, black=Controls, green=Etoricoxib+H56:IC31

**Supplementary Figure 4. Cytokine responses for all study groups at all time points.** Descriptive line plots of different cytokine responses measured by Fluorospot at day 0 to day 238 with median and IQR for all study groups; etoricoxib-group (red; n=10), H56:IC31-group (blue, n=12), controls (black, n=10) and etoricoxib+H56:IC31 group (green, n=8) are depicted for Cytokine+ T-cells to individual *Mtb*

peptides (ESAT-6, Ag85B and CFP-10) (first 3 panels), IFN $\gamma$ +IL2+ T-cells in response to ESAT-6+Ag85B+CFP-10 (fourth panel) and ESAT-6+Ag85B (sixth panel) and finally IFN $\gamma$ + T-cells in response ESAT-6+Ag85B.

Supplementary Figure 5

a

[figure not shown]

b

[figure not shown]

[figure not shown]

**Supplementary Figure 5. Immunogenicity of the H56:IC31 vaccine.** Effect of the H56:IC31-vaccine administered at two doses (day 84 and day 140) on vaccine-induced immunity in the H56:IC31 group (blue, n=12) and controls (grey, n=10) (Hypothesis 2, table 3) at day 84 and day 154. Cytokine responses (IFN $\gamma$  and IL-2) to H56 fusion protein and the individual peptides (ESAT-6 and Ag85B) are measured by Fluorospot assay. **a** IFN $\gamma$  T-cell responses to the H56 fusion protein in the H56:IC31 group and controls at day 84 (n: 12/10) and day 154 (n: 11/10). Boxplots are shown with median, interquartile ranges (IQR) and minimum/maximum values. Median regression with treatment as only independent explanatory factor was applied for immunogenicity read-outs pre-assigned a hierarchical order to compensate for lack of multiple testing adjustments. Effect estimates of primary priority and 95% confidence intervals based on 1000 bootstrap replications and corresponding two-sided p-values depicted in Table 3 (main paper) and denoted in **a**. **b** Descriptive line plots with median and IQR, and individual trajectories at different time points during follow-up for both H56:IC31 and control group.

## Supplementary Figure 6

[figure not shown]

**Supplementary Figure 6. Adjunctive effects of etoricoxib on H56:IC31 immunogenicity.** H56:IC31-vaccine administered at two doses (day 84 and day 140) in the etoricoxib+H56:IC31-group (green, n=8) and the H56:IC31 group (blue, n=12) and (Hypothesis 3, table 3) at day 84 and day 154. IFN $\gamma$  T-cell responses to H56 fusion protein are measured by Fluorospot assay. **a** IFN $\gamma$  T-cell responses to the H56 fusion protein in the etoricoxib+H56:IC31-group and the H56:IC31 group at day 84 (n: 8/12) and day 154 (n: 7/11). Boxplots are shown with median, interquartile ranges (IQR) and minimum/maximum values. Median regression with treatment as only independent explanatory factor was applied for immunogenicity read-outs pre-assigned a hierarchical order to compensate for lack of multiple testing adjustments. Effect estimates of primary priority and 95% confidence intervals based on 1000 bootstrap replications and corresponding two-sided p-values depicted in Table 3 (main paper) and denoted in **a**. **b** Descriptive line plots with median and IQR, and individual trajectories at different time points during follow-up for both H56:IC31 and control group.

## Supplementary Figure 7

[figure not shown]

**Supplementary Figure 7. Adjunctive effects of etoricoxib on H56:IC31 immunogenicity.** H56:IC31-vaccine administered at two doses (day 84 and day 140) in the etoricoxib+H56:IC31-group (green, n=8) and the H56:IC31 group (blue, n=12) (Hypothesis 3, table 3) at day 84 (n: 8/12) and day 154 (n: 7/11). Cytokine responses (IL-2 and IL-2+ IFN $\gamma$ ) to H56 fusion protein and the individual peptides (ESAT-6 and Ag85B) are measured by Fluorospot assay. Descriptive line plots with median and IQR, and individual trajectories at different time points during follow-up for the etoricoxib+H56:IC31-group and the H56:IC31 group.

Supplementary Figure 8

Whole blood intracellular cytokine staining (WB-ICS) assay

red=Etoricoxib, blue=H56:IC31, black=Controls, green=Etoricoxib+H56:IC31

Cytokine+ CD4 T cell responses to PPD

[figure not shown]

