## Priority ranking of immunogenicity readouts according to statistical plan

### Definition of outcomes described in Tables 1-3

- **Sin cytokine:** Cells expressing only one cytokine: sin\_IFN $\gamma$  or sin\_IL2 or sin\_TNF $\alpha$ .\*
- **Duo cytokine:** Cells expressing two cytokines simultaneously: duo\_IFN $\gamma$ /IL2 or duo\_IFN $\gamma$ /TNF $\alpha$ \*or duo\_IL2/TNF $\alpha$ .\*
- **Tri cytokines:** Cells expressing three cytokines simultaneously: tri\_IFN $\gamma$ /IL2/TNF $\alpha$ .\*
- **Tot cytokines:** SUM of cytokine combinations expressing cytokine of interest (sin\_cytokines PLUS duo\_cytokines PLUS tri\_cytokines\*): tot\_IFN $\gamma$  or tot\_IL2 or tot\_TNF $\alpha$ \*
- **All cytokines for Whole Blood ICS (Cytokine+):** SUM of the following cytokine combinations: tot\_IFN $\gamma$  PLUS duo\_IL2/TNF $\alpha$  PLUS sin\_IL2 PLUS sin\_TNF $\alpha$ .
- **All cytokines for Fluorospot (Cytokine+):** SUM of the following cytokine combinations: tot\_IFN $\gamma$  PLUS tot\_IL2 MINUS duo\_IFN $\gamma$ /IL2.:

**Supplementary Table 3.** Hierarchal ranking of primary and secondary priority outcomes and definition of hypotheses that will be tested comparing etoricoxib vs. controls. Formal testing will be performed on the primary priority outcomes only, tertiary priority outcomes are not listed here.

| Method                                           | Outcome/readout                                                             | Time interval (days) | Comparison           |
|--------------------------------------------------|-----------------------------------------------------------------------------|----------------------|----------------------|
| Primary priority                          |                                                                             |                      |                      |
| FLUOROSPOT (FS)                                  | All_cytokine responses to SUM (Ag85+ESAT6+CFP10)                            | 0-84                 | Group (1+4) vs (2+3) |
|                                                  | Tot_IFN $\gamma$ responses to SUM (Ag85+ESAT6+CFP10)                        | 0-84                 | Group (1+4) vs (2+3) |
| Whole blood (WB) intracellular cytokine analyses | All_cytokine CD4 responses to PPD                                           | 0-84                 | Group (1+4) vs (2+3) |

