### Secondary endpoints: immunogenicity read-outs

We used descriptive statistics (medians and IQR) to describe all pre-defined immunogenicity readouts at each study time point. In the IgG assay, we also described the number and proportion of vaccine seroconverters in each group defined as an increase in H56 IgG-responses of  $>2$ -fold from day 84 to any time point after.

Immunogenicity read-outs of primary priority for Hypothesis 1 were responses to treatment defined as the change from day 0 to day 84 in the defined outcomes (**Table 3**). The outcomes were analyzed using median regression with treatment as only independent explanatory factor. The treatment difference of the combination of both groups allocated to etoricoxib (etoricoxib-group and etoricoxib+H56:IC31-group) and the combination of controls and the H56-IC31-group (vaccine not administered until day 84) were calculated as estimated difference in median response with 95% confidence interval based on 1000 bootstrap replications and corresponding two-sided p-value. For Hypothesis 2 and Hypothesis 3, immunogenicity read-outs of primary priority were responses to vaccine treatment defined as the change from day 84 to day 154 (**Table 4 and 5**). The seed for the bootstrap replications was set to 20200316 (pre-defined as the date of the final statistical analysis plan (Version 1.0)).

Exploratory post-hoc analyses were performed for immunogenicity readouts predefined as secondary and tertiary priority from day 84 to day 154 using the same statistical analyses as for the primary priority read-outs described above.

Data were collected in the eCRF Viedoc™ version 4.66.7823.20827 and Microsoft Excel 2016. Statistical analyses were performed in STATA version 16 (StataCorp) and figures drawn in GraphPad Prism version 7.02.

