## **10.4 Statistical Analysis**

Groups will be compared with non-parametrical statistical methods throughout with two-ways tests using p-values equal to or below 0.05 as significant. No adjustments due to multiple comparisons will be performed.

Deviation from the original statistical plan will be described and justified in the Clinical Study Report. The investigators can make the decision regarding individual values belonging to a subject to be excluded from the statistical evaluations, but only when a protocol violation is considered to weaken any of the scientific aspects of the study. Missing data will not be substituted by estimated values, but will be treated as missing data by the method used.

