##### **10.4.6.1 Primary Immunogenicity endpoints**

The primary variables of interest for assessment of immune response to vaccine will be the percentage of CD4+ and CD8+ T cells that produce any of selected cytokines. The immunogenicity of H56:IC31 in this study will be evaluated by PBMC ICS, T-cell proliferation and IL-2/IFN- $\gamma$  ELISPOT. Due to the exploratory nature of immunogenicity endpoints, the primary evaluation will be based on descriptive summaries and no formal hypothesis testing will be performed.

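### The priority ranking of immunogenicity read-outs is said to compensate for unadjusted testing, but it has no stopping rule and leaves the false-positive rate of the 14 primary-priority tests unchanged

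*Protocol*

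**What the plan says.** Supplementary Tables 3-5 sort the immunogenicity read-outs into priority tiers for three hypotheses. The caption of Table 3 speaks of a "definition of hypotheses that will be tested comparing etoricoxib vs. controls" and attaches one restriction: "Formal testing will be performed on the primary priority outcomes only, tertiary priority outcomes are not listed here". Tables 4 and 5 carry the same restriction.

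The section on secondary endpoints (immunogenicity read-outs) analyses each primary-priority read-out by median regression, with a bootstrap interval and a two-sided p-value. It then reports exploratory post-hoc analyses of read-outs "predefined as secondary and tertiary priority from day 84 to day 154 using the same statistical analyses as for the primary priority read-outs".

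Three statements describe the role or status of these tests:

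- Section 10.4 sets "two-ways tests using p-values equal to or below 0.05 as significant" and adds: "No adjustments due to multiple comparisons will be performed".
- Section 10.4.6.1 says that for the immunogenicity endpoints "the primary evaluation will be based on descriptive summaries and no formal hypothesis testing will be performed".
- The legends of Supplementary Figures 5 and 6 say the read-outs were "pre-assigned a hierarchical order to compensate for lack of multiple testing adjustments". The Supplementary Figure 3 legend is milder: the order "was judged adequate to assign importance/interpret the results of the respective statistical tests". That legend also says that no adjustment was made and that p-values are not read as confirmation.

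**The concern.** Compensating for missing adjustment is a claim about error rates. An ordered list delivers it only as a gate, where testing stops at the first failure. Without a gate, every read-out in the tier is tested whatever happened above it, and the error rate is that of ungated tests.

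The legends of Figures 5 and 6 make the claim where p-values are shown, and they do not repeat the caveat from Figure 3. A reader may give those p-values more weight than the procedure earns. The status of the p-values is also unclear, because one section declares tests at 0.05, another says there is no formal testing, and the tables announce formal testing.

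**Working it through.** The Protocol states no family-wise error rate, so there is no figure of its own to reproduce.

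**Counts, from Supplementary Tables 3-5**

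| Hypothesis | Comparison | Primary-priority rows |
|---|---|---|
| 1 | Groups 1+4 vs 2+3, days 0-84 | 2 Fluorospot + 2 whole blood = 4 |
| 2 | Group 2 vs 3, days 84-154 | 3 Fluorospot + 1 whole blood + 1 IgG = 5 |
| 3 | Group 4 vs 2, days 84-154 | 3 Fluorospot + 1 whole blood + 1 IgG = 5 |

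Total: 4 + 5 + 5 = 14.

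**Search for a gate.** The table captions, the section on secondary endpoints and section 10.4 contain no condition that makes one test depend on another, within or between tables.

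**Independent tests at 0.05, no true effect.** Chance of at least one positive = 1 − 0.95^m:

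- m = 4: 1 − 0.8145 = 0.185
- m = 5: 1 − 0.7738 = 0.226
- m = 14: 1 − 0.4877 = 0.512

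Expected false positives over the 14 tests: 14 × 0.05 = 0.70.

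**Allowing for dependence.** The read-outs overlap. The Fluorospot all-cytokine measure includes total IFN-gamma by definition, H56 contains Ag85B and ESAT-6 (section 1.2.3), and Group 2 serves both Hypotheses 2 and 3. A normal-approximation simulation used 200,000 replicates, full-analysis-set sizes 10, 12, 10 and 8 for arms 1 to 4, the shared Group 2, and an assumed equal correlation between read-outs within each time interval. The Protocol gives no correlation.

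| Assumed correlation | Hyp. 1 | Hyp. 2 | Hyp. 3 | All 14 |
|---|---|---|---|---|
| 0 | 0.184 | 0.226 | 0.226 | 0.498 |
| 0.3 | 0.174 | 0.210 | 0.207 | 0.469 |
| 0.5 | 0.155 | 0.183 | 0.184 | 0.423 |
| 0.7 | 0.130 | 0.147 | 0.149 | 0.356 |
| 0.9 | 0.094 | 0.102 | 0.103 | 0.260 |

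A separate run at correlation 0.8 gave about 13% for five tests and 31% for all 14. At correlation 0, the all-14 figure is 50% rather than 51% because of the shared Group 2. The ranking enters none of these calculations, so it lowers none of the results.

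**Lower tiers.** Tables 4 and 5 each list 13 secondary rows. Four of these combine CD4 and CD8, so split there are 17. Expected false positives per hypothesis: 13 × 0.05 = 0.65 to 17 × 0.05 = 0.85. Tertiary read-outs are not listed and cannot be counted.

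**What a gate would give.** One fixed sequence over all 14 tests holds the family-wise error at 0.05. Three separate sequences at 0.05 give 1 − 0.95³ = 0.143 (0.138-0.140 simulated).

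**The case against.** The best defence is that the trial is openly exploratory. It has no sample-size calculation, its primary endpoint is safety without formal testing, the absence of adjustment is declared, and the Figure 3 legend rules out a confirmatory reading. Fixing the tiers in advance also curbs selective emphasis. All of this stands, and it justifies not adjusting. It does not make the compensation claim in Figures 5 and 6 true.

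Two further points stand as limits. The 0.05 threshold is stated in section 10.4 for non-parametric group comparisons, while the description of the median regressions gives p-values without a threshold; applying 0.05 to the 14 tests is a reasonable inference, not a quotation. And the family-wise figures describe the chance of at least one positive. A reader might infer that any single positive read-out is enough to call a hypothesis supported, but no section sets that success rule.

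A reader might also infer that the later testing cancelled the restriction to the primary tier. The Protocol does not support that in full: the lower-tier analyses are labelled exploratory and post hoc, and they are reported for days 84-154 only, with none for Hypothesis 1.

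**Conclusion.** The compensation claim in the legends of Supplementary Figures 5 and 6 is wrong as written. The 14 primary-priority tests keep their unadjusted error. With no true effect and 0.05 per test, that is about 13-23% within Hypothesis 2 or 3 (correlation 0.8 to 0) and about 26-51% across all 14 (correlation 0.9 to 0, the upper end assuming full independence). The correlations are assumptions. The listed secondary tier adds about 0.65-0.85 expected false positives for each of Hypotheses 2 and 3.

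It would go too far to call this a failure of confirmatory error control, since the Protocol claims none. It is a false justification for secondary endpoints in an exploratory trial, together with an unresolved conflict over whether formal testing takes place.

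**What to change.** 1. In the legends of Supplementary Figures 5 and 6, replace the compensation clause with the position of the Figure 3 legend: the ranking only helps to weigh and interpret results, and the p-values are unadjusted and not confirmatory.
2. Beside the p-values, state how many tests were run per hypothesis and per tier. Give any family-wise error only as a range, with the correlation assumptions stated.
3. Reconcile section 10.4 (tests at 0.05), section 10.4.6.1 (no formal hypothesis testing) and Supplementary Tables 3-5 (formal testing of the primary tier) so that the status of each p-value is clear.
4. Use a fixed-sequence gate only if an order within the primary tier was fixed before results were known. The rows there are grouped by assay and not stated to be ranked. With results already reported, a gate chosen now would be retrospective, and three separate gates would still leave about 14% overall.

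Items 1 to 3 change wording only and need no new data or re-analysis. The cost is that the p-values will look less protected than the legends now suggest.

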**Cytokine+ CD4 T cell responses to Ag85B, ESAT-6 and Rv2660c**

[figure not shown]

**Cytokine+ CD4 T cell responses to ESAT-6**

[figure not shown]

**Cytokine+ CD4 T cell responses to Ag85B**

[figure not shown]

**Cytokine+ CD4 T cell responses to Rv2660c**

[figure not shown]

**IFN $\gamma$ +IL2+TNF $\alpha$ + CD4 T cell responses to Ag85B, ESAT-6 and Rv2660c**

[figure not shown]

**IFN $\gamma$ +IL2+TNF $\alpha$ + CD4 T cell responses to ESAT-6**

[figure not shown]

### IFN $\gamma$ +IL2+TNF $\alpha$ + CD4 T cell responses to Rv2660c

[figure not shown]

### IFN $\gamma$ +IL2+TNF $\alpha$ + CD4 T cell responses to Ag85B

[figure not shown]

**IFN $\gamma$ +IL2+TNF $\alpha$ - CD4 T cell responses to Ag85B, ESAT-6 and Rv2660c**

[figure not shown]

**IFN $\gamma$ +IL2+TNF $\alpha$ - CD4 T cell responses to ESAT-6**

[figure not shown]

### IFN $\gamma$ +IL2+TNF $\alpha$ - CD4 T cell responses to Ag85B

[figure not shown]

### IFN $\gamma$ +IL2+TNF $\alpha$ - CD4 T cell responses to Rv2660c

[figure not shown]

### IFN $\gamma$ -IL2+TNF $\alpha$ + CD4 T cell responses to ESAT-6

[figure not shown]

### IFN $\gamma$ -IL2+TNF $\alpha$ + CD4 T cell responses to Ag85B

[figure not shown]

IFN $\gamma$ -IL2+TNF $\alpha$ + CD4 T cell responses to Rv2660c

[figure not shown]

IFN $\gamma$ -IL2+TNF $\alpha$ + CD4 T cell responses to Ag85B, ESAT-6 and Rv2660c

[figure not shown]

**IFN $\gamma$ +IL2-TNF $\alpha$ + CD4 T cell responses to Ag85B, ESAT-6 and Rv2660c**

[figure not shown]

**IFN $\gamma$ +IL2-TNF $\alpha$ + CD4 T cell responses to Rv2660c**

[figure not shown]

